#### Randomization

To avoid bias, participants will be individually randomized to the *Re-train Your Brain* integrated group, the *Re-train Your Brain* alternating group, or the control group (on a 1:1:1: basis) via the trial website using a computer-generated randomization sequence, which is concealed from the investigators. This process removes the potential for researcher involvement. Randomization will occur directly after the completion of the online baseline cognitive assessment (Figure 1).

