### Statistical Analysis and Power Calculations

As this is a pilot trial, a formal power calculation is not required [81,82]. The pilot trial is essential to determine the expected size of effect, which will be used to inform the sample size of a future definitive RCT aiming to assess the efficacy of the *Re-train Your Brain* program. Rates of attrition will be used to indicate estimated follow-up rates in future trials. On the basis of several rules of thumb used to determine an appropriate sample size for a pilot study [83-85], a sample size of 90 young people (30 per arm) was selected to provide sufficient data on the feasibility, acceptability, and preliminary efficacy of the program, although we recognize that the scope of this pilot trial does not allow for a fully powered test of efficacy. Data will be collated and analyzed using StataCorp data analysis software [86].

Descriptive statistics for primary and secondary outcomes will be conducted based on frequencies and cross-tabulations. Analyses for secondary (preliminary) efficacy outcomes will use multilevel mixed effects analysis for repeated measures, which is a flexible analytic approach for modeling change over time using RCT data [87,88]. All models will use baseline measurements as the reference point to estimate participant-specific starting points and change over time. The intervention condition will be represented by a dummy-coded variable, and the condition by time interaction will be examined to assess between-group differences in outcomes over time. Analyses will be consistent with an intention-to-treat framework, with all randomized participants included in the analysis models, regardless of training completion or loss to follow-up. Missing data will be accommodated in these models using maximum likelihood estimation. Preliminary models will be estimated, with model fit statistics examined to determine the most appropriate model and covariance structure. Cohen *d* will be calculated from model-estimated marginal means and SEs to determine the size of the effect between conditions at the relevant end point. In addition, effect sizes will be analyzed as a function of session completion (ie, completion of six or more training sessions, given that this has been identified as the mean optimum number of ApBM sessions in past research [67]).

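### Cohen d, as described, is an end-point difference not adjusted for baseline and scaled from model SEs, so it carries avoidable noise and a denominator that moves with missing data

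*Protocol article*

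**What the plan says.** All of the relevant text is in the protocol article, section Statistical Analysis and Power Calculations, unless noted.

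- Role of baseline: "All models will use baseline measurements as the reference point to estimate participant-specific starting points and change over time".
- Fixed effects: "The intervention condition will be represented by a dummy-coded variable, and the condition by time interaction will be examined". The purpose of that interaction is given as "the condition by time interaction will be examined to assess between-group differences in outcomes over time".
- Effect size: Cohen d is calculated "from model-estimated marginal means and SEs to determine the size of the effect between conditions at the relevant end point". The standardising SD, and the n that would turn an SE into an SD, are not named.
- Missing data: "Missing data will be accommodated in these models using maximum likelihood estimation".
- Size: "a sample size of 90 young people (30 per arm) was selected". The Randomization section gives allocation to the two programs "or the control group (on a 1:1:1: basis") and mentions no stratification by baseline severity.
- Use of the result: "The pilot trial is essential to determine the expected size of effect, which will be used to inform the sample size of a future definitive" trial.

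**The concern.** With baseline as the reference time, the condition dummy is the arm difference at baseline and the interaction is the arm difference in change. The end-point difference in marginal means is their sum. The contrast that is examined and the effect size that is reported are therefore two different estimators, and neither is adjusted for baseline in the sense of an analysis of covariance. Participant-specific starting points do not remove a difference between arm means at baseline.

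Separately, a model SE is not an SD. Converting one to the other requires a choice of n, and the result changes with the amount of missing data.

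What is at stake is the planning value of the pilot. A noisier and inconsistently scaled d goes into the sample size of the definitive trial, and a reader may meet an interaction and a d that point in different directions.

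**Working it through.** **Inputs.** From the article: 30 per arm, 3 arms, 3 visits (baseline, 6 weeks, 3 months). The only sample-size figure checks as 3 × 30 = 90; no alpha, power or target effect is stated, so there is nothing further to reproduce. Assumptions: correlation ρ between baseline and follow-up of 0.5 to 0.7 (not in the documents), equal SD at each visit, a separate mean per arm and visit, and follow-up missing completely at random. The illustrative 34.2% missing is the general figure for web-based interventions cited under Strengths and Limitations, not a design assumption of this trial. All results are in SD units.

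**1. Chance baseline difference b.** SD(b) = √(2/30) = 0.258. P(|b| > 0.25) = 2 × [1 − Φ(0.25/0.258)] = 0.33 per pairwise comparison.

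**2. How much reaches d.** Given b, the end-point difference has expectation δ + ρb and the difference in change has expectation δ − (1 − ρ)b. One SD of imbalance moves the end-point difference by ρ × 0.258 = 0.129, 0.155 and 0.181 for ρ = 0.5, 0.6 and 0.7. A simulation of the three-arm model with complete data (1,500 trials per setting) gave slopes on b of 0.47, 0.61 and 0.69. With a common baseline mean the slopes were within 0.03 of zero. For a true effect of 0.50 the unconstrained estimate averaged 0.495 to 0.500, so there is no bias.

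**3. Disagreement in sign.** With complete data the two contrasts have variances 2/n and 4(1 − ρ)/n and covariance 2(1 − ρ)/n. From the bivariate normal distribution they have opposite signs in about 24% of comparisons for a true effect of 0.2 SD and about 14–16% for 0.3 SD (both effects assumed).

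**4. Precision, complete data.**

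| ρ | SE end point, √(2/n) | SE change, √(4(1−ρ)/n) | SE adjusted, √(2(1−ρ²)/n) | 95% half-width, end point → adjusted |
|---|---|---|---|---|
| 0.5 | 0.258 | 0.258 | 0.224 | 0.51 → 0.44 |
| 0.6 | 0.258 | 0.231 | 0.207 | 0.51 → 0.40 |
| 0.7 | 0.258 | 0.200 | 0.184 | 0.51 → 0.36 |

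With 34.2% missing and ρ = 0.6, the simulated SD of the end-point contrast was 0.302 unconstrained and 0.256 with a common baseline mean.

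**5. SD recovered from an SE.** With a fraction m missing, Var(end-point mean) = SD²(1 − ρ²m)/n_obs. The implied SD, relative to the true SD, is √[(1 − ρ²m)/(1 − m)] using n = 30 and √(1 − ρ²m) using the observed n.

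| m | n used | ρ 0.5 | ρ 0.6 | ρ 0.7 |
|---|---|---|---|---|
| 34.2% | 30 | 1.179 | 1.154 | 1.125 |
| 34.2% | observed | 0.956 | 0.936 | 0.912 |
| 10% | 30 | 1.041 | 1.035 | 1.028 |
| 10% | observed | 0.987 | 0.982 | 0.975 |

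At 34.2% missing, d is multiplied by 0.85–0.89 in the first case and by 1.05–1.10 in the second.

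**6. Effect on the next trial.** For 80% power and two-sided 5%, n per arm = 2(1.960 + 0.842)²/d². A true d of 0.5 gives 62.8, so 63. At ρ = 0.6 and 34.2% missing, d is scaled by 1/1.154 = 0.866 or 1/0.936 = 1.068, giving 62.8/0.866² = 83.7 (84) or 62.8/1.068² = 55.1 (56). These design values are illustrative.

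**7. Adjusting for baseline but keeping the SE route.** With complete data, SE × √30 would be √(1 − 2ρ²/3) = 0.91–0.82 of the SD under a common baseline mean over three arms, and √(1 − ρ²) = 0.87–0.71 with a baseline covariate. That would inflate d by 10–22% or 15–40%.

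**The case against.** The strongest reply is that the model is not fully specified. The article leaves the final form to preliminary fits and fit statistics, and the analysis plan is not shown. If that plan constrains the baseline means or includes baseline as a covariate, the imbalance and precision points disappear. This stands as a condition. But the article does state a reference time, a dummy, an interaction and a way to compute d, and nothing in it indicates adjustment.

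A reader might infer that d estimates something different from the interaction, or is biased. It does not and is not: randomisation makes the expected baseline difference zero, so the matter is variance.

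A reader might also infer that the baseline measurement is wasted, or that these d values are the trial's whole efficacy result. Neither is supported. The interaction uses baseline, maximum likelihood draws on it when follow-up is missing, and interaction analyses and descriptive statistics are also planned. Nor can chance imbalance be called as large as the plausible effects, because the article gives no plausible effect and only ρ times the imbalance reaches d.

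On the denominator, it is fair to say that the article never writes SE × √n, that 34.2% is not this trial's expected loss, and that several retention strategies are planned. At 10% missing the shift is small. What remains is that SEs are named as the source of the effect size, and any SD taken from them depends on n and on missingness.

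**Conclusion.** The point holds as a matter of precision and consistency, not of bias. On the model as described, d carries about 0.13 to 0.18 SD of noise per one-SD chance imbalance. Its complete-data SE is 0.258 SD, where 0.224 to 0.184 is available from data already collected, and it can disagree in sign with the interaction in a given sample. The SE-based denominator adds a scaling error of about 12–18% upward or 4–9% downward at 34.2% missing, and about 1–4% at 10%.

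The sizes rest on the assumed ρ of 0.5–0.7, equal SDs and data missing completely at random. The first two parts also rest on the full plan containing no baseline adjustment. Primary outcomes are feasibility and acceptability, so this affects the pilot's value for planning and not its primary conclusions. It should be changed because the gain is free.

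**What to change.** 1. Estimate the arm contrasts at 6 weeks and 3 months from a model with a common baseline mean across arms, or with baseline as a covariate. The common-mean form keeps participants with no follow-up in the model, which fits the stated aim of including everyone randomised.
2. Report each adjusted difference in raw units with its 95% CI, and derive d from that same contrast, so that the test and the effect size agree.
3. Standardise by the observed pooled baseline SD, not by an SD derived from model SEs. Adopt this together with step 1, because SE-based SDs after adjustment would inflate d.
4. For the Alcohol Use Disorder Identification Test, where eligibility requires a score of at least 8, name the SD used and note the restricted range. Give d with the observed follow-up SD as a sensitivity check, acknowledging that it depends on who is followed up. The two social anxiety short forms do not need the same treatment: eligibility is met on either scale, so neither has a hard floor of its own.

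The cost is analysis wording and model code. No additional data, visits or participants are needed.

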## Results

Recruitment is expected to be completed by mid-2022 to late 2022, with the 6-week and 3-month follow-ups to be completed by early 2023. The results are expected to be submitted for publication in 2023. The research team intends to present the findings of this trial at professional seminars and national and international conferences. Only aggregated group data will be reported, and no individuals will be identified.

## Discussion

### Principal Findings

This paper presents the design of the *Re-train Your Brain* study, a randomized controlled pilot trial seeking to evaluate the feasibility, acceptability, and preliminary efficacy of a 10-session, web-based ApBM+IBM brain training program for hazardous alcohol use and social anxiety among young Australians aged 18-30 years, when combined with TAU. To the best of our knowledge, this is the first study to evaluate a comorbidity-targeted intervention of this kind, using a cost-effective, web-based delivery method.

### Strengths and Limitations

This study has several strengths. First, the intervention was co-designed with emerging adults who have direct lived experience of hazardous drinking and social anxiety and clinicians who have experience treating anxiety and/or alcohol use concerns. This bottom-up approach, whereby emerging adults and clinicians were involved in the development of the methodology and stimuli used within the intervention (eg, the alcoholic or nonalcoholic beverages used in ApBM and the scenarios included in IBM), was critical to ensuring that the program is relevant, engaging, and useful for end users. This codevelopment process also helps to ensure that the program can be feasibly implemented and is responsive to the needs of service providers.

An additional strength of this study is the web-based delivery of the interventions. The *Re-train Your Brain* intervention is simple, inexpensive, and can be self-administered via the internet without any specific skills or knowledge. This format allows for easy and convenient access anywhere and at any time (eg, in the privacy of one’s home), thereby offering a larger outreach and greater availability. It is also being investigated in the setting in which it is most likely to be implemented, if proven effective in a future RCT. On theoretical and practical grounds, incorporation of a web-based psychoeducational or motivational enhancement-type module at the outset of training will aid its efficacy and will also likely boost engagement and user buy-in. It may also increase treatment adherence and reduce study attrition. Thus, the web-based delivery of this program has the potential to enhance clinical outcomes at a minimum cost in terms of time and effort for both patients and service providers.

Finally, despite their high co-occurrence, to date, most CBM programs have addressed anxiety and alcohol use in isolation of one another, with a few exceptions for attention bas modification [48]. The current intervention is unique in that it combines effective alcohol ApBM and anxiety IBM-focused protocols to optimize standard treatments among a young comorbid sample. Given the interconnections between anxiety and alcohol use problems, whereby each disorder fuels the other and impedes recovery from the other, it is possible that combining these programs will have incremental (or synergistic) effects on anxiety and alcohol use outcomes in a vulnerable group that responds poorly to standard treatments [10,89].

One of the main strengths of this study is also its main limitation: that is, its web-based delivery. First, internet interventions are conducted in a less-controlled home environment that may pose several online distractions (eg, email notifications) and offline distractions (eg, housemates or phone calls), which have the potential to impact the study results. Second, web-based interventions also have higher rates of attrition compared with standard face-to-face treatments (eg, 34.2% vs 24.6%, respectively) [90]. Further increasing the risk of attrition, CBM interventions are inherently repetitive and as such are sometimes considered boring because of the monotonous nature of the tasks [28,91]. To help overcome these limitations, at the start of each session, participants are reminded of the importance of conducting training in a quiet environment where they can concentrate for a 20-minute block. To leverage on participants’ intrinsic motivation for change and maximize their initial buy-in, a compelling rationale and motivational enhancement module is provided at the outset of the program. These components will set expectations about the purpose and nature of the intervention (eg, computerized and repetitive training), which will likely enhance motivation to train and, thus, result in increased adherence and lower attrition. In addition, multiple evidence-based strategies to minimize treatment and study attrition will be used, such as monetary incentives, email and SMS text messaging reminders, and explanation of the importance of completing the sessions and follow-up surveys to participants [79,80]. Taken together, the possible threats presented by the web-based delivery of the intervention are outweighed by the possibilities and benefits it may offer.

Furthermore, this study uses a control group that receives TAU and zero training, rather than a control group that is matched for both stimulus exposure (ie, time spent completing the ApBM and IBM tasks) and response requirements. Sham control-training groups are considered the optimal comparator groups for these reasons and because participants remain blind to their group allocation [92]. However, some research has shown that there is no significant difference between experimental and sham control groups (as both groups improve [33,92]), suggesting that sham training may in fact have an active component rather than it being a *neutral* or *placebo* training it is intended to be. This is particularly the case for online trials and less so for laboratory-based trials [47]. This way, it is conceivable that both online-delivered sham and experimental conditions represent placebo effects; however, this cannot be ruled out in a two-arm design (active vs control training). Given that this study is a pilot trial with primary outcomes focused on feasibility and acceptability (as opposed to efficacy) and secondary outcomes on preliminary efficacy, an active control group could mask any possible intervention effects, and thus, a no-training group was selected as the comparator. Indeed, in this study, priority was given to testing two experimental varieties on top of TAU, as compared with TAU. Future RCTs aiming to evaluate the clinical efficacy of this hybrid intervention may consider a different three-arm design, comparing the ApBM+IBM intervention against both an (active) sham-training control and a zero training control condition (ie, TAU), and examine potential mediation effects across the three conditions.

### Conclusions and Implications

This world’s first hybrid ApBM+IBM training program combines the best elements of efficacious ApBM training programs for alcohol use problems and IBM for social anxiety into a hybrid program for emerging adults who experience both of these problems. This innovative program can be delivered over the internet and can thereby maximize efficiency and scarce resources and sustainably increase the intervention options for vulnerable populations at a low cost. Given the costs of conducting an RCT, it is important to establish whether the *Re-train Your Brain* ApBM+IBM program is acceptable to emerging adults and whether it is feasible to deliver via the internet, in settings where it will ultimately be used and easily scaled to, including at home. The pilot trial findings will contribute to understanding the types of programs that emerging adults will engage with and whether there are signs of it being an efficacious treatment option for this comorbidity.

## Appendix

Multimedia Appendix 1 A detailed description and interpretation of scores for primary and secondary outcome measures.

## Abbreviations

ApBM: approach bias modification
CBM: cognitive bias modification
CONSORT: Consolidated Standards of Reporting Trials
IBM: interpretation bias modification
RCT: randomized controlled trial
SPIRIT: Standard Protocol Items: Recommendations for Interventional Trials
TAU: treatment as usual
